### Assignment of interventions: allocation

#### Sequence generation {16a}

To ensure an equal distribution of patient characteristics and confounders between the two groups, a randomisation tool will be used. Randomisation will be performed at the patient level with a centralised online randomisation system (www.randomizer.at). The online randomisation procedure provides information regarding the group allocation and a randomisation number. The randomisation sequence is computer-generated and will be stratified by centre and presence/absence of neoadjuvant treatment. Block randomisation will be performed. The randomisation procedure will be performed intraoperatively (after surgical exploration) after the fulfilment of all intraoperative inclusion criteria.

#### Concealment mechanism {16b}

As randomisation in the TRIANGLE trial depends on the intraoperative inclusion criteria and the findings during the exploratory phase of surgery, the allocation to the assigned group will be performed intraoperatively after fulfilling the inclusion criteria. Allocation concealment is therefore not necessary, as the assigned intervention will be performed immediately after randomisation.

#### Implementation {16c}

The randomisation will be performed intraoperatively by a member of the study team after fulfilling all of the intraoperative inclusion criteria by using the online randomisation tool. Names of the randomising study team member as well as the team of surgeons will be documented. They will not be involved in the outcome assessment.

### Assignment of interventions: blinding

#### Who will be blinded {17a}

Patients and outcome assessors will be blinded to the intervention in order to guarantee an unbiased assessment of the primary and secondary endpoints. The outcome assessors will be neither part of the surgical team that performs the trial intervention nor have access to the randomisation tool. All patient-reported outcomes (PROs) will be assessed using validated measures. Moreover, the discharge letter will contain no information regarding group allocation.

#### Procedure for unblinding if needed {17b}

If unblinding is necessary due to medical conditions, it can be performed by the treating physicians or one of the unblinded study team members. Unblinding will be documented and reported to the steering group of the trial.

### Data collection and management

#### Plans for assessment and collection of outcomes {18a}

All of the included trial sites will be high-volume centres with broad expertise in pancreatic surgery as well as the conduction of clinical trials. Most of the centres are part of the CHIR-Net, which has successfully performed trials with similar indications and recruitment rates in the past [34–36].

To further enhance data quality and to minimise detection bias, validated measures and classifications will be used where possible (see the “Outcomes {12}” section). Additionally, the primary outcome (DFS) is an objective measure defined “as the time from randomisation until disease recurrence or death from any cause” according to international guidelines [22].

#### Plans to promote participant retention and complete follow-up {18b}

As outlined above, all of the included trial sites will be experienced in the conduction of randomised trials with similar indications and follow-up procedures. Furthermore, pancreatic cancer patients are in need of an oncological follow-up that usually is performed in high-volume centres. If follow-up is not performed in the centres, visits after discharge of the patients can also be done by telephone including a collection of the necessary data.

#### Data management {19}

An eCRF will be used for data collection. The study data will be collected using REDCap [37] (Research Electronic Data Capture), a secure, web-based data capture application hosted at the IMBI. To assure a safe and secure environment for the data acquired, data transmission is encrypted with secure socket layer (SSL) technology. The database server is located in a secure data centre and is protected by a firewall. The system provides an infrastructure to support user roles and rights. Only authorised users are able to enter or edit data; the access is restricted to data of the patients in the respective centre. All changes to data are logged with a computerised timestamp in an audit trial. All clinical data will be pseudonymised. Backups are conducted regularly.

All protocol-required information collected during the trial must be entered by the investigator or designated representative in the eCRF. For health-related quality of life and patient-reported outcome data, patients may directly enter the data in the eCRF. Alternatively, paper-based reported outcome questionnaires must be entered by the investigator or designated representative in the eCRF. The investigator or designated representative should complete the eCRF forms as soon as possible after information is collected, preferably on the same day that a trial subject is seen for an examination, treatment, or any other trial procedure. Any outstanding entries must be completed immediately after the final examination. An explanation should be given for all missing data. The completed eCRF must be reviewed and signed by the local investigator or by a designated sub-investigator.

To guarantee high data quality, data validation rules will be defined in a data validation plan. Completeness, validity and plausibility of data will be checked at the time of data entry (edit checks) and using validating programs, which will generate queries. The investigator or the designated representatives are obliged to clarify or explain the edit checks and queries. If no further corrections are to be made in the database, eCRF data will be locked.

All data collected will be integrated into a statistical analysis system. During study conduct, database access will be granted to the data manager only. After database closure, access rights will be granted to the biometricians as well. The data will be managed and analysed in accordance with the appropriate standard operating procedures (SOPs) valid in the IMBI Heidelberg that guarantee an efficient conduct complying with Good Clinical Practice (GCP). Photo files from the surgery are collected at each local site and are stored according to the applicable local, national and international regulations.

#### Confidentiality {27}

Patients will be informed as to the strict confidentiality of their data, but that their medical records may be reviewed for trial purposes by authorised individuals (trial monitor) other than their treating physician. It is the responsibility of the investigator to maintain patients’ confidentiality. During the trial, patients will be identified solely by means of their individual identification codes. Trial-specific documents will be stored in accordance with local data protection law/ICH-GCP Guidelines and will be handled in the strictest confidence. For the protection of these data, organisational procedures are implemented to prevent the distribution of data to unauthorised persons. The patients’ data will be transferred in a pseudonymised form from the trial centre to cooperating partners (coordinating investigator, data management). Names and all confidential data of participating patients will be handled in line with the obligations of medical secrecy, the European General Data Protection Regulation (Datenschutzgrundverordnung, DSGVO), the Federal Data Protection Act (Bundesdatenschutzgesetz) and the state Data Protection Act (Landesdatenschutzgesetz). Participating patients’ data will be documented in the eCRF only in pseudonymised form. Decoding of the pseudonymised data is only permitted in justified cases. Third parties have no access to original documents. After completion of the trial, data collected during the study will be kept on file for 10 years. It is guaranteed that the data protection provisions are followed. The sponsor provides data protection management and an information security management system. The Clinical Trial Centres are contractually obliged to comply with the DSGVO and other data protection regulations.

#### Plans for collection, laboratory evaluation and storage of biological specimens for genetic or molecular analysis in this trial/future use {33}

There are no plans for the collection, laboratory evaluation and storage of biological specimens for genetic or molecular analysis in the TRIANGLE trial.

## Statistical methods

### Statistical methods for primary and secondary outcomes {20a}

The primary outcome disease-free survival is compared between the groups using a Cox proportional hazards model adjusted for the covariates treatment group, age, neoadjuvant treatment, adjuvant treatment as fixed effects and centre as a random effect. It can be expected that applying the Cox proportional hazards model will lead to an increase in power in comparison with a log-rank test. Confounding by other less important prognostic and predictive factors can be assumed to be controlled by the randomised trial design. The significance level is set to 5% (two-sided). The confirmatory analysis is conducted based on the full analysis set (FAS) according to the ITT principle, i.e. all randomised patients are included and analysed in the treatment group as randomised which reflects a treatment policy approach (according to the ICH E9 (R1) addendum). Death, as an intercurrent event occurring after randomisation, is handled by inclusion into the definition of the primary endpoint which reflects a composite strategy.

All secondary outcomes will be evaluated descriptively, and descriptive *p*-values for the corresponding effects will be reported along with 95% confidence intervals. Continuous variables will be described using a number of missing values, non-missing values, mean, standard deviation, median, Q1, Q3, minimum and maximum. For binary or categorical variables, absolute and relative frequencies will be provided. Thereby, binary and categorical variables will be compared by the chi-squared tests, and continuous variables will be compared with *t*-tests. OS will be analysed analogously to the primary endpoint with a Cox proportional hazards model. QoL will be analysed using linear mixed models with baseline score, age, treatment group and the stratification variables as covariates; centre and time point will be included as random effects. Furthermore, the treatment effect for secondary endpoints will be assessed descriptively within several subgroups to identify potential prognostic and predictive factors. Analyses of secondary endpoints will be based on the ITT population. No imputation of missing values will be conducted in the analyses of secondary endpoints.

Baseline characteristics will be analysed descriptively with appropriate statistical measures. Further details of the analysis will be specified in the statistical analysis plan (SAP) which will be finalised before database closure. All calculations will be done using SAS version 9.4 or higher.

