### Outcomes {12}

#### Primary endpoint

The primary endpoint of the TRIANGLE trial will be the DFS after resection, defined “as the time from randomisation until disease recurrence or death from any cause” [22]. Disease recurrence can be a local recurrence or distant metastases. Given the overall dismal prognosis of PDAC, the high rate of recurrence as well as the objective of the trial, i.e. to reduce recurrence rates and improve OS, DFS seems the logical and most relevant endpoint for the TRIANGLE trial. It is a frequent endpoint in cancer trials in the adjuvant setting after definitive surgery, and it is widely accepted by regulatory authorities worldwide [22, 23] and has been used in previous randomised controlled trials (RCTs), thus allowing the comparison of data between trials [16, 24, 25]. Furthermore, it is based on objective and quantitative assessments. DFS is patient-relevant as it includes all-cause mortality and recurrence. In order to avoid detection bias, follow-up will be standardised for both groups and include clinical outpatient visits, contrast-enhanced CT scan and tumour markers every 6 months for 3 years.

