Intervention effect: Possible intercurrent events and the strategies to handle them are as follows: Death, as an intercurrent event occurring after randomisation, is handled by inclusion into the definition of the primary endpoint which reflects a composite strategy. Patients with incomplete observation time due to loss to follow-up or early drop-out will be censored at the last observation, which reflects a hypothetical strategy. Besides these events, other post-randomisation events (e.g. intervention not as randomised, discontinuation of chemotherapy) will not be considered, thus reflecting a treatment policy approach, which means that the effect of randomised treatment is estimated irrespectively of other post-randomisation events not captured in the primary endpoint definition. This corresponds to the intention-to-treat (ITT) principle.

Summary measure: The summary measure is the adjusted hazard ratio.

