### Methods in analysis to handle protocol non-adherence and any statistical methods to handle missing data {20c}

The confirmatory analysis of the primary endpoint will be conducted according to the ITT principle which reflects a treatment policy approach according to the ICH E9 (R1) addendum. Patients with incomplete observation time due to loss to follow-up or early drop-out will be censored at the last observation (hypothetical strategy). Further post-randomisation events will be ignored. This also reflects a treatment policy approach. Because of the use of the Cox approach, no missing values in the primary endpoint will occur. Furthermore, no missing values in the covariates of the Cox model are expected.

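### The confirmatory Cox model conditions on adjuvant treatment, a post-randomisation variable, and so does not estimate the treatment-policy effect that the protocol defines

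*Protocol article*

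**What the plan says.** In the protocol article, the section on statistical methods for primary and secondary outcomes {20a} specifies a Cox model for the primary endpoint "adjusted for the covariates treatment group, age, neoadjuvant treatment, adjuvant treatment as fixed effects and centre as a random effect". It calls this analysis confirmatory at the two-sided 5% level and describes it as following treatment policy. Overall survival takes the same form: "OS will be analysed analogously to the primary endpoint with a Cox proportional hazards model".

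Three other places fix the timing and the target:

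- **Sequence generation {16a}:** "The randomisation procedure will be performed intraoperatively (after surgical exploration) after the fulfilment of all intraoperative inclusion criteria".
- **Primary endpoint:** disease-free survival is defined "as the time from randomisation until disease recurrence or death from any cause".
- **Primary estimand:** apart from death and incomplete follow-up, "other post-randomisation events (e.g. intervention not as randomised, discontinuation of chemotherapy) will not be considered, thus reflecting a treatment policy approach". It adds that "the effect of randomised treatment is estimated irrespectively of other post-randomisation events not captured in the primary endpoint definition".

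The section on non-adherence and missing data {20c} repeats the rule: "Further post-randomisation events will be ignored. This also reflects a treatment policy approach". The concomitant care section {11d} leaves all additional treatment to the treating physician. The additional analyses section {20b} plans an unadjusted Cox model as a sensitivity analysis only.

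**The concern.** Age, centre and neoadjuvant treatment are settled before randomisation. Adjuvant treatment is not. Whether a patient receives it depends on recovery from the operation, on pathology, and on being alive and free of recurrence when it would start. The operation under test may influence all of these.

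The Discussion shows plausible routes. Diarrhoea was 53.6% versus 5.9% in the preceding single-centre trial and 34.4% versus 14.4% in the retrospective comparison. R1 resection was 31.4% versus 42.9% (not significant).

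If the operation changes who receives adjuvant treatment, part of its effect on disease-free survival runs through that treatment. Holding adjuvant status fixed removes that part. The trial's one confirmatory hazard ratio would then answer a question other than the stated one, and a test of it need not keep the 5% level for the treatment-policy null.

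**Working it through.** **1. The plan's own figure.** Schoenfeld events with 1:1 allocation: d = 4(z₀.₉₇₅ + z₀.₈₀)² / (ln HR)². For HR 0.667 this is 4 × (1.960 + 0.842)² / (0.405)² ≈ 191.4, so 192, as the sample size section states. No covariate enters this formula.

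**2. What the two quantities are.** Write Z for arm and A for adjuvant receipt. The planned model is h(t) = h₀(t)·exp(βZ + γA + …), so exp(β) compares arms among patients with the same A. The treatment-policy effect compares arms with A left to fall as it does in each. They differ whenever Z changes A and A changes the hazard.

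**3. A hand check of direction.** Suppose there is no direct surgical effect and the adjuvant hazard ratio is 0.6. With uptake p, the average hazard just after adjuvant start is proportional to 0.6p + (1 − p).

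- 80% control, 60% experimental: (0.36 + 0.40) / (0.48 + 0.20) = 0.76 / 0.68 = 1.12.
- 70% control, 80% experimental: (0.48 + 0.20) / (0.42 + 0.30) = 0.68 / 0.72 = 0.94.
- Equal uptake: 1.00.

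Over whole follow-up these shrink towards 1, because adjuvant treatment starts only at month 2 and the higher-hazard untreated patients leave the risk set sooner.

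**4. Simulation.** From the protocol: 270 patients, 1:1, control median about 14 months, drop-out 20% at 66 months, follow-up of at least 36 months. Assumed: the uptake figures (fitness for adjuvant treatment), adjuvant hazard ratio 0.6 from month 2, and ever/never coding. Ranges reflect separate runs, with and without an unmeasured frailty affecting both fitness and disease-free survival. The 80/70 row and the last row are with frailty only. False benefit means a significant result favouring TRIANGLE (nominally at most 2.5%).

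| Direct HR | Uptake, control / experimental | HR without adjuvant | HR with adjuvant | False benefit with adjuvant |
|---|---|---|---|---|
| 1 | 80 / 80 | about 1.0 | 0.99–1.01 | no bias in the HR |
| 1 | 80 / 70 | 1.03–1.04 | 0.91 | 11–12% |
| 1 | 80 / 60 | 1.07–1.08 | 0.84–0.90 | 12–27% |
| 1 | 70 / 80 | about 0.96 | 1.05–1.10 | direction reversed |
| 0.667 | 80 / 60 | 0.76–0.77 | 0.57–0.58 | not applicable |

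**5. Where the 80/60 gap comes from.** With ever/never coding, a patient whose event precedes adjuvant start must be coded as untreated (immortal time), which pushes the adjusted value below the direct effect of 1. It is about 0.90 without frailty and 0.84 with it. Time-dependent coding gives 0.98 and 0.94. That is nearer the direct effect, but still not the total effect of 1.07–1.08.

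**6. Type I error without frailty or immortal time.** Here adjuvant status acts from time zero and the total effect is set to null. With uptake 70% versus 50–60% and adjuvant hazard ratio 0.5–0.7, the model without adjuvant gives 0.99–1.01 and rejects in 4–5% of trials. The model with it gives 0.88–0.97 and rejects in 6–15%.

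**The case against.** The strongest defence has five parts.

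- **No evidence of differing uptake.** The protocol gives no adjuvant uptake by arm. The Discussion reports comparable serious adverse events in the earlier trial, otherwise comparable perioperative morbidity in the retrospective series, and diarrhoea that is often treatable. With equal uptake the null hazard ratio is unbiased. This stands. A reader might infer that the primary result is certainly biased in TRIANGLE's favour, or that the 5% level is already lost. The documents support neither; if uptake were higher after TRIANGLE, the model would understate its benefit.
- **Coding is left open.** The model names adjuvant treatment without saying how it is coded, and the analysis plan may settle that. This also stands, so the larger figures above are not properties of the written plan. Time-dependent coding would reduce the distortion but would still condition on a mediator.
- **The summary measure is declared to be an adjusted hazard ratio.** That permits adjustment for baseline factors. It does not reconcile conditioning on later treatment with an effect defined irrespective of later events. The estimand's named example is stopping chemotherapy rather than receiving it, but its clause covers all other post-randomisation events.
- **An unadjusted model is planned.** It would expose a discrepancy. It does not carry the confirmatory claim, and it also drops age and neoadjuvant treatment.
- **Adjustment gains power.** In runs with equal uptake and a direct hazard ratio of 0.667, adding adjuvant raised the rejection rate from 79.6% to 83.4%, from 81.5% to 82.7% and, with frailty, from 68.3% to 75.7%. The 192 events do not rely on this gain.

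A reader might also set the statement that "no missing values in the covariates of the Cox model are expected" against patients who die before adjuvant treatment could start. That does not hold up: such a patient can be coded as not having received it. Early drop-outs leave at most a small gap, which is a matter for the analysis plan.

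**Conclusion.** The point holds as a contradiction between estimand and model. It follows from the text alone: randomisation is intraoperative, adjuvant treatment comes afterwards, later events are to be ignored, and the confirmatory model conditions on one of them.

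The numerical consequence is conditional. If adjuvant uptake differs by arm, the primary hazard ratio is biased for the stated estimand and the type I error may be inflated. Under the assumptions listed, a 20-point fall in uptake after TRIANGLE moves a total hazard ratio of about 1.07–1.08 to 0.84–0.90. A 10-point rise moves about 0.96 to 1.05–1.10. Uptake by arm, the adjuvant effect, the frailty and the coding are all assumptions, so neither size nor direction can be stated for this trial.

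Overall survival inherits the model, but its analysis is descriptive, so no confirmatory error rate is at stake there. Because the covariate sits in the only confirmatory test, the change should be made before the analysis plan is finalised.

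**What to change.** Delete adjuvant treatment from the confirmatory disease-free survival model, and from the overall-survival model that copies it. Keep treatment group, age and neoadjuvant treatment as fixed effects and centre as a random effect. Report receipt and timing of adjuvant treatment by arm descriptively. Label any model that adjusts for it as exploratory, with its own stated target.

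The cost is one line in the protocol, carried into the analysis plan. It needs no new patients, and 192 events and n = 270 stand because they rest on a log-rank test without covariates. What is given up is any precision that the adjuvant covariate would have added; the remaining baseline covariates can still supply some.

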## Introduction

### Background and rationale {6a}

Pancreatic ductal adenocarcinoma (PDAC) is the fourth most frequent cause of cancer-related death in the Western world, and its incidence is rising [1, 2]. Survival differs widely depending on the tumour stage and surgical resection via pancreatoduodenectomy (PD) in case of tumours of the pancreatic head is one of the mainstays in the treatment of PDAC and the only option for curative treatment [3–5]. The rise of more efficient chemotherapeutic regimes like FOLFIRINOX or Gem/nabPac in recent years, has led to an increased use of neoadjuvant treatments raising the hope that more patients will qualify for potential curative resection in the future [6].

However, local recurrence (LR) is frequent following surgical resection for PDAC, and prognosis is significantly worse for patients experiencing LR compared to non-LR [7].

Several independent risk factors predict LR, one of which is the status of the pathological resection margin. The R0 resection rate has been proposed as a quality indicator for pancreatic surgery [8, 9] and has shown to be an important prognostic parameter not only for local recurrence but can also improve overall survival (OS) as well as disease-free survival (DFS) in PDAC patients [10].

Owing to the perineural growth pattern of PDAC, R1 resections occur most frequently along the soft tissue margins towards the celiac and superior mesenteric artery (i.e. medial margin) [11, 12]. Therefore, by applying more radical dissection techniques along the superior mesenteric artery (SMA) and the celiac artery (CA), marginal clearance can be improved.

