### Eligibility criteria {10}

The following are the preoperative inclusion criteria for patients:Patients with suspected or histologically verified resectable, borderline or locally advanced pancreatic cancer of the pancreatic head (i.e. pancreatic ductal adenocarcinoma, intraductal papillary mucinous neoplasm (IPMN)-carcinoma or periampullary cancer of the pancreatobiliary-type)Patients scheduled for elective partial pancreatoduodenectomy (irrespective of neoadjuvant therapy)Assumed resectability in accordance with the surgical protocol for experimental and control intervention as judged by the treating surgeonAbility of the subject to understand character and individual consequences of the clinical trialWritten informed consentAge ≥ 18 years

The following are the intraoperative inclusion criteria for patients (prior to randomisation):No distant metastasesNo paraaortic lymph node metastasesIntraoperative confirmation that the patient can be operated on according to both surgical methods (experimental or control group)

The following are the exclusion criteria for patients:Participation in another interventional trial with the interference of intervention and outcome of this trialAmerican Society of Anesthesiologists (ASA) grade > 3Distant metastatic disease

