### Methods for additional analyses (e.g. subgroup analyses) {20b}

As a sensitivity analysis in the meaning of the ICH E9 addendum, the primary estimand will also be analysed by the unadjusted Cox proportional hazards model. As supplementary analyses, the primary endpoint will also be evaluated based on the per-protocol (PP) population including only those patients without major protocol violations and based on the as-treated set the same way as in the confirmatory analysis. Furthermore, the treatment effect will be assessed descriptively within several subgroups to identify potential prognostic and predictive factors. In addition, further covariables are included and analysed in the primary analysis model in order to identify further possible influencing factors.

For safety analysis, all SAEs will be analysed via descriptive statistical methods. The safety analysis includes calculation of frequencies and rates of complications and serious adverse events together with corresponding 95% confidence intervals. For comparisons of frequencies between the groups, the chi-square test will be used.

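### The confirmatory DFS model leaves out baseline resectability class; prespecifying it would be a cheap, optional gain in power

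*Protocol article*

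**What the plan says.** All references are to the protocol article.

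- **Statistical methods {20a}** sets the primary DFS model: Cox regression "adjusted for the covariates treatment group, age, neoadjuvant treatment, adjuvant treatment as fixed effects and centre as a random effect". For everything not listed it states: "Confounding by other less important prognostic and predictive factors can be assumed to be controlled by the randomised trial design". Overall survival is to be analysed in the same way.
- **Eligibility criteria {10}** admits "resectable, borderline or locally advanced pancreatic cancer of the pancreatic head".
- **Background and rationale {6a}** says: "Survival differs widely depending on the tumour stage".
- **Sequence generation {16a}**: allocation is "stratified by centre and presence/absence of neoadjuvant treatment". Both stratification factors are in the model; resectability class is neither a stratum nor a covariate.
- **Additional analyses {20b}**: "further covariables are included and analysed in the primary analysis model in order to identify further possible influencing factors". These covariables are not named and lie outside the confirmatory test.
- **Sample size {14}** rests on an unadjusted log-rank test. Both {14} and {20a} expect the Cox model to add power.

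**The concern.** In a Cox model, the power gain over a log-rank test comes from baseline covariates that predict outcome. At patient level this model has two: age and neoadjuvant treatment. Adjuvant treatment follows randomisation and is not a baseline factor. Tumour extent before surgery is an obvious further candidate, and the protocol's own background makes it hard to place among the less important factors. Neoadjuvant treatment may capture part of it, but it need not coincide with class.

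At stake is some of the power that the protocol expects from adjustment. In addition, the reported hazard ratio would be conditional on fewer predictors and so somewhat nearer to 1.

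**Working it through.** **1. The plan's own figure.** Inputs from Sample size {14}: HR 0.667, two-sided 5%, power 80%, 1:1 allocation. Schoenfeld: d = 4(1.960 + 0.842)² / (ln 0.667)² = 31.4 / 0.1640 = 191.4, rounded up to **192**, as stated. Power at 192 events is 80.1%. No covariate enters this figure.

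**2. Which hazard ratio to simulate.** If each class has exponential survival and treatment multiplies every class hazard by the same HR, then S₁(t) = S₀(HR × t). The ratio of overall medians is then the conditional HR: 14/21 = 0.667. So 0.667 is a fair conditional value for a mixed population with the protocol's medians.

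**3. Assumptions, not in the documents.** Class mix is 50/30/20% (resectable / borderline / locally advanced), with a range of relative hazards. Neoadjuvant use is either linked to class (10/60/95%) or not linked (40% in each class).

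**4. Simulation A.** 2,000 trials per scenario, n = 270, follow-up 36 to 66 months, exponential drop-out of 20% at 66 months, mean control hazard ln 2/14 per month. Both models contain treatment and neoadjuvant use; the second adds class.

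| Relative hazards | Neoadjuvant use | HR without → with class | SE of log HR | Power, % | Gain, points |
|---|---|---|---|---|---|
| 1/1.2/1.5 | linked | 0.667 → 0.663 | 0.1376 → 0.1386 | 85.5 → 85.0 | −0.5 |
| 1/1.2/1.5 | not linked | 0.670 → 0.665 | 0.1376 → 0.1386 | 83.7 → 84.6 | +0.9 |
| 1/1.5/2 | linked | 0.672 → 0.664 | 0.1386 → 0.1397 | 82.2 → 83.9 | +1.7 |
| 1/1.5/2 | not linked | 0.679 → 0.663 | 0.1385 → 0.1397 | 79.9 → 82.8 | +2.9 |
| 1/2/3 | linked | 0.686 → 0.667 | 0.1411 → 0.1424 | 75.8 → 81.6 | +5.8 |
| 1/2/3 | not linked | 0.696 → 0.663 | 0.1408 → 0.1424 | 73.4 → 82.3 | +8.9 |

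Each power figure has a Monte Carlo standard error of about √(0.8 × 0.2/2,000) = 0.9 points, so gains or losses under one point should not be read as real.

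**5. Simulation B.** Same mix and number of trials, but overall medians set to 14 and 21 months and every patient followed for 36 months. Power without → with class, linked / not linked:

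- 1/1.2/1.5: 80.6 → 80.9 / 80.3 → 81.2
- 1/1.5/2: 79.1 → 80.4 / 79.1 → 82.4
- 1/2/3: 73.8 → 79.6 / 71.2 → 79.1

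The gains are +0.3 to +7.9 points, in line with A.

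**6. Where the gain arises.** Take the last row of A. Without class, |ln 0.696|/0.1408 = 2.57, and Φ(2.57 − 1.96) = 73%. With class, |ln 0.663|/0.1424 = 2.89, and Φ(2.89 − 1.96) = 82%. The standard error rises by about 1%; the log HR moves further from zero by more than that.

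**Limit.** Age, adjuvant treatment and a centre effect were not simulated.

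**The case against.** The case for leaving the model alone is reasonable. The covariates are prespecified, both stratification factors are included, and the choice of further prognostic factors is a design judgement. Several stronger readings that a reader might infer fail:

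- *The omission loses precision.* It does not: in every scenario of simulation A the standard error is slightly smaller without class.
- *The hazard ratio is biased.* The shift is non-collapsibility. The estimand is a hazard ratio adjusted for the listed covariates, and conditioning on one more changes the quantity estimated.
- *Chance imbalance invalidates the comparison.* With a 20% locally advanced share, the arms can differ by about 1.96 × √(2 × 0.2 × 0.8/135) = 9.5 points, but randomisation protects type I error and the standard error already allows for this.
- *The trial is undersized.* The 192 events take no credit from any covariate.
- *Class is known to be strong here.* The background remark concerns pancreatic cancer generally. Patients are randomised only after metastases are excluded and operability by both techniques is confirmed, which may narrow the spread.
- *Class is already recorded.* Eligibility names the three classes but admits all of them, and Table 2 does not list class as a visit 1 item.

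All six limits stand. The further covariables in {20b} let class be examined, but they add nothing to the confirmatory test. The covariate list itself is stated in the article, so this is not merely a detail left to the SAP.

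**Conclusion.** The point holds as an optional improvement, not as an error or a contradiction in the analysis. The protocol's background sits uneasily with treating tumour extent as one of the less important factors, and adding class costs little.

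Under the assumed 50/30/20% mix and with neoadjuvant treatment in the model, the gain is about 0 to 3 power points for relative hazards up to 1/1.5/2, with the HR moving by 0.004 to 0.016. It is about 6 to 9 points for 1/2/3, with the HR moving by 0.019 to 0.033. No scenario showed a material loss. The upper range depends on a strong class effect for which the documents give no figure, so it should not be quoted as the expected gain.

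**What to change.** Before any outcome data are seen, add preoperative resectability class (three levels) as a fixed effect in the primary DFS model and the analogous overall-survival model. Define it as assessed before randomisation and at one stated time point for all patients; for pretreated patients, say whether that is before or after neoadjuvant therapy. Make it a mandatory visit 1 field, so that the expectation of no missing covariates in {20c} remains tenable. For any patient already randomised, take it from preoperative records by someone blinded to allocation. Update the adjusted hazard ratio in the estimand to match; the unadjusted sensitivity analysis can stay.

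The cost is a line in the analysis section, one eCRF field, two degrees of freedom against 192 events, a standard error of the log HR about 1% larger, and partial overlap with the neoadjuvant covariate. Sample size and randomisation strata do not change.
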